#### 2.11.2. Secondary Outcome Variable

Data on the incidence of falls at one month, six months, and one year after the health education intervention will be collected.

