## 4. Detailed Procedure

This study has two arms, an intervention and a control arm. Participants from PCFs assigned to the intervention arm would receive the group educational intervention, while participants from PCFs in the control group would receive care as usual. Participants will be assessed for eligibility based on the inclusion and exclusion criteria at the nurses’ office. In cases where the patient agrees to participate and meets the criteria, a screening visit will be conducted to confirm compliance. Screening sheets will be kept for those participants who do not meet the criteria or do not wish to participate.

Patients will be followed up for 12 months. Data collection visits will take place at baseline, one month, six months, and 12 months.

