### 4.3. Visit Plan

During the study period, both study groups will make the following visits (see Table 2):-Initial visit: screening.-Pre-intervention baseline visit: Collection of data on variables. Approximate duration: 60–80 min. The patients assigned to the control group shall carry it out up to two weeks before the beginning of the initial health education intervention.-Five initial sessions with the intervention group.-Visit post initial intervention (visit window: ±4–8 weeks after randomization (for the control group) or ±2 weeks after the initial sessions (for the intervention group)): Collection of data on variables. Approximate duration: 25 min.-Visit at six months post initial intervention (visit window: ±2–4 weeks, at six months after randomization (for the control group) or after the initial health education intervention (for the intervention group)), always prior to the booster session. Collection of data on variables. The structured education plan proposed in the Portfolio of Services will be reviewed in both groups, as well as in the patients in the intervention group, including a follow-up of the issues identified during the health education intervention. Approximate duration: 45 min.-Booster session with the intervention group.-Visit at 12 months (visit window: ±2–4 weeks, at 12 months post randomization in the control group or at 6 months after the booster session in the intervention group). Collection of data on variables. Approximate duration: 20 min.

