For the secondary outcome variable (incidence of falls), a process similar to the main analysis will be followed, but this time fitting a fixed-effects logistic regression model, again nesting each facility within its group. The effectiveness of the health education intervention for the incidence of falls will be measured through the recording of falls (recorded in the medical history or reported by the patient), at 1-, 6- and 12-months post intervention. Both groups will be compared in terms of odds ratios, and their corresponding 95% confidence intervals will be provided.

To assess the impact of the health education intervention by time, mixed effects models will be adjusted, including time also as an independent variable and random intercepts for participants.

Data will be recorded in a paper data collection notebook and entered into an Excel spreadsheet by a single researcher in order to minimize the risk of transcription errors. The collected data will then undergo a second review to correct transcription errors, if necessary. Access to these data will be limited to authors until open access dissemination, after which they can be included on ClinicalTrials.gov.

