### Limitations

This study features a number of drawbacks. Firstly, a selection bias may be introduced during recruitment at PCFs. The recruitment of participants who are visiting their healthcare professionals could influence the results. However, it is not possible to recruit them randomly using databases, as there are no registers of patients with FOF. Secondly, given the nature of this study, the health education intervention cannot be blinded to participants. Thirdly, the validity of the data to be extracted from health records could be underestimated in cases with poor documentation. Finally, participants will be recruited only in the Autonomous Community of Madrid due to financial and human resources constraints, which may limit the generalizability of the results.

Difficulties may also be encountered when implementing this study, as it is an health education interventional trial with four scheduled visits, in which attrition rates may be high due to dropouts, non-attendance, or non-compliance with instructions. To mitigate this problem, we aim to maximize patient retention through regular telephone calls, in which appointments will be arranged with participants prior to each interview. Furthermore, an additional 20% of participants will be recruited to accommodate for potential losses.

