## Figures and Tables

**Figure 1 healthcare-12-02510-f001:**
[figure not shown]
CONSORT flowchart of participants.

**Table 1 healthcare-12-02510-t001:** Short FES-I scale.

Short FES-I Scale How Concerned Are You About the Possibility of Falling While…?	Not at All Concerned	Somewhat Concerned	Fairly Concerned	Very Concerned
1. Getting dressed or undressed	1 □	2 □	3 □	4 □
2. Taking a bath or shower	1 □	2 □	3 □	4 □
3. Getting in or out of a chair	1 □	2 □	3 □	4 □
4. Going up or down stairs	1 □	2 □	3 □	4 □
5. Reaching for something above your head or on the ground	1 □	2 □	3 □	4 □
6. Walking up or down a slope	1 □	2 □	3 □	4 □
7. Going out to a social event (e.g., religious service, family gathering or club meeting)	1 □	2 □	3 □	4 □
SUBTOTAL:	Add all the 1’s	Add all the 2’s	Add all the 3’s	Add all the 4’s
	Short FES-I ≥ 11: Fear of falling			

**Table 2 healthcare-12-02510-t002:** Summary of visits and variables.

Variables	Visits						
	Initial Visit. Screening	Pre-Intervention Baseline visit ^1^	Five Initial Group Sessions	Visit Post Initial Intervention ^2^	Visit at Six Months Post Initial Intervention ^3^	Booster Session	Visit at 12 Months ^4^
Review of eligibility criteria	x						
Informed consent	x	x					
Primary outcome variable: Short FES-I		x		x	x		x
Secondary outcome variable: Post intervention falls		x		x	x		x
EXPLANATORY VARIABLES							
Sociodemographic variables		x					
Functional variables		x			x		
Usual footwear		x			x		
Clinical variables		x					
Falls during intervention				x		x	
Ability to practice self-care		x		x	x		x
Perceived health and anxiety		x		x	x		x
Acceptability (among patients)				x			

^1^ ±2 weeks before the health education intervention (for the intervention group: (IG)). ^2^ ±2 weeks after the initial sessions (IG). ±4–8 weeks after randomization (for the control group (CG)). ^3^ ±2–4 weeks, at six months after randomization (CG) or after the initial health education intervention (IG), always prior to the booster session. ^4^ ±2–4 weeks, at 12 months post randomization (CG), at six months after the booster session (IG).

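### Cheap improvement: falls rest on the medical history or patient report at 1, 6 and 12 months; a dated falls calendar in both arms would shorten recall without adding visits

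*Protocol article*

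**What the plan says.** Section 2.11.2 makes falls the secondary outcome: "Data on the incidence of falls at one month, six months, and one year after the health education intervention will be collected". The abstract lists fall incidence among the primary outcomes. Section 4.4 gives the source and timing, "recorded in the medical history or reported by the patient), at 1-, 6- and 12-months post intervention", and compares the arms by odds ratios.

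The contact points are few. Section 4 states: "Data collection visits will take place at baseline, one month, six months, and 12 months". Table 2 has a row headed "Secondary outcome variable: Post intervention falls", marked at baseline and at the three follow-up visits. It also has a row for falls during the intervention, marked at the visit after the initial sessions and at the booster session. Only the intervention arm attends the booster.

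On data quality, the Limitations section says that "the validity of the data to be extracted from health records could be underestimated in cases with poor documentation". On contact between visits it says: "we aim to maximize patient retention through regular telephone calls, in which appointments will be arranged with participants prior to each interview". It does not say that these calls ask about falls. No diary, calendar or other running record is described. Section 2.11 refers to Supplementary File S1 for the assessment tools, and that file was not available.

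**The concern.** A fall that leads to care may enter the medical history when it happens. A fall without injury, for which no care is sought, reaches the outcome only if the participant remembers it at the next visit. Such falls therefore depend on recall over months, and the other named source is one that the article itself describes as possibly poorly documented.

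The trial is open after recruitment (section 2.9), so under-recall need not be equal. The intervention arm is offered five two-hour sessions plus a booster, with fall prevention among the topics (section 4.1). In intervention centers the assessment interviews and the sessions are both run by local participating nurses (section 2.5), so the roles may overlap. The visit clocks also differ by arm (section 4.3).

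At stake is the falls comparison. Lost events make an already imprecise result weaker. Unequal loss could look like benefit or harm where there is none.

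**Working it through.** **Plan's own figure.** No sample size or power is stated for falls. The sample size in section 2.7 is for the short FES-I. It reproduces under a normal approximation: effective n per arm = 5 × 12 / (1 + 11 × 0.1) = 60 / 2.1 = 28.6, which gives 80.4% power for 3.8 points with SD 5.1, and 120 / 0.8 = 150. A change in how falls are collected leaves it untouched.

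**Recall gaps.** From the stated time points: 6 − 1 = 5 months and 12 − 6 = 6 months. Section 4.3 shows that the gaps are not the same in both arms. The first follow-up visit is "4–8 weeks after randomization (for the control group") or within "2 weeks after the initial sessions (for the intervention group"). Taking six months as 26 weeks and leaving aside the windows around the later visits:

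| Gap | Control | Intervention |
|---|---|---|
| First to six-month visit | 26 − (4 to 8) = 18-22 weeks | 26 − (0 to 2) = 24-26 weeks |
| Six-month to 12-month visit | about 26 weeks | at least about 26 weeks, as it runs from the booster, which follows the six-month visit |

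**Effect on the odds ratio.** Let p be the true proportion of fallers and s the share of fallers captured, with I for intervention and C for control. Then

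OR seen = [p_I s_I / (1 − p_I s_I)] / [p_C s_C / (1 − p_C s_C)].

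The values of s are assumptions, because the documents give none. The 25% v 35% contrast is illustrative. The 30-40% annual incidence used in the null case is the article's own (Introduction).

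*Equal capture, true 25% v 35%:*
- s = 1: 0.333 / 0.538 = 0.62
- s = 0.9: (0.225/0.775) / (0.315/0.685) = 0.290 / 0.460 = 0.63
- s = 0.7: (0.175/0.825) / (0.245/0.755) = 0.212 / 0.325 = 0.65

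The loss is 10-30% of fallers, but the odds ratio barely moves.

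*Unequal capture, no true effect:*

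| True p | 90% v 80% | 90% v 70% |
|---|---|---|
| 30% | (0.27/0.73)/(0.24/0.76) = 1.17 | (0.27/0.73)/(0.21/0.79) = 1.39 |
| 40% | (0.36/0.64)/(0.32/0.68) = 1.20 | (0.36/0.64)/(0.28/0.72) = 1.45 |

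If the better-captured arm is the control arm, these become 0.85, 0.72, 0.84 and 0.69.

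**Effect on precision.** Illustration with 60 per arm, 35% fallers in control, a risk ratio of 0.7, a two-sided 5% two-proportion test and clustering ignored: power for falls is 24% at full capture, 19% at 80% and 17% at 70%.

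**The case against.** The strongest counter-case has five parts.

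- **Unseen detail.** Section 4.4 does not say how the patient reports, and Supplementary File S1 might describe a tool. An article may leave that out. This stands as a caveat: the point concerns what the article describes.
- **Records between visits.** A reader might infer that nothing records falls between visits. The documents do not support that, because the medical history is a named source and can be written at the time. What remains exposed is the fall that never reaches care. The booster entry in Table 2 does not close the gap: it comes after the six-month visit and adds a fall enquiry in one arm only.
- **Size.** Equal under-recall hardly changes the odds ratio, and the larger figures come from assumed differences of 10 to 20 percentage points. This stands. The faller yes/no analysis also needs only one captured fall per person. In addition, many control patients are offered structured education that includes fall prevention (section 4.2), so the contrast in awareness may be smaller than it looks.
- **Power.** Even complete capture leaves the illustrative power at 24%. Recording is not what mainly limits the falls comparison.
- **The remedy.** A reader might infer that a calendar captures every fall as it happens. That does not follow: pages can be filled in just before the visit, and completion can differ by arm in an open trial. The planned calls, as described, fall shortly before each interview and so prompt late in each gap.

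These points limit the claim. They do not show the stated method to be as good as a dated record kept close to the event.

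**Conclusion.** The point holds as a cheap improvement, not as an error in the plan. As section 4.4 states it, falls that are not brought to care depend on recall over about five and six months in an open trial, and the gaps differ somewhat between arms. Attenuation from equal under-recall is negligible (0.62 to 0.63-0.65 at an assumed 70-90% capture), although 10-30% of fallers are lost. The main risk is differential recall: an odds ratio of 1.17-1.45 or 0.69-0.85 with no true effect, if capture is 90% in one arm and 70-80% in the other. A reader might infer from this that the falls result will be biased in a known direction. The documents give no recall figure for either arm, so neither size nor direction can be stated.

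The conclusion does not depend on whether falls are primary, as in the abstract, or secondary, as in the body. It would lapse if Supplementary File S1 already provides a prospective record.

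**What to change.** In sections 2.11.2 and 4.4 and in Table 2:

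- Give every participant in both arms a monthly falls calendar at baseline, on which any fall is marked with its date.
- Collect it at the existing 1-, 6- and 12-month visits.
- Use the telephone calls already planned to give the same reminder in both arms.
- Make the calendar the main source of the outcome, with the visit question and the medical record as back-up.
- Report calendar completion by arm.

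The cost is printed pages and a few minutes per visit or call. No visit, staff member or participant is added, and the sample size and significance level do not change. The downside is a small participant burden and pages left incomplete or filled in late, possibly more in one arm. The calendar therefore reduces recall error without removing it, and completion by arm lets readers judge how much may remain.

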### 4.4. Data Analysis

A descriptive analysis by groups (intervention and control) of participants’ sociodemographic, functional, and clinical characteristics will be carried out to identify potential differences between the two study groups, with quantitative variables expressed as either means and standard deviations or medians and interquartile ranges depending on the normality or skewness of data distribution. Qualitative variables will be summarized as frequencies and percentages. Data on the effect of the health education intervention will be analyzed in both the intention-to-treat population and the per-protocol population. In the former case, all participants will be included and will be analyzed as part of the group to which their PCF will be randomly assigned. Should the percentage of missing data be higher than 5%, multiple imputation techniques will be used. In the per-protocol analysis, complete cases of patients will be included provided they have maintained adherence. The intervention group is required to be adherent and have at least 80% attendance at the initial five sessions. Safety, acceptability, and feasibility of the health education intervention will also be assessed.

The primary efficacy analysis, (FOF), will be the comparison between intervention and control groups fitting a fixed-effects ANOVA model. Model will include group and facility as independent variables, with facility being a nested factor within group. The short FES-I scale mean scores and their 95% confidence intervals will be provided for each facility, or by groups if no differences between facilities are observed. The effectiveness of the health education intervention in relation to fear of falling will be measured through the decrease in the short FES-I scale scores, assessed at three times: at 1-, 6- and 12 months after the intervention. The difference in means between the intervention and control groups will be analyzed. In addition, the variable will be examined dichotomously, using a cut-off point on the short FES-I scale of 11 or more to identify the presence of fear of falling. Multivariate models will be fitted to identify factors potentially related to FOF.

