## 5. Expected Results

The purpose of this study is to explore the possibility of improving FOF and the incidence of falls in community-dwelling people over 65 years of age through a group educational intervention carried out by nurses. This is the first study conducted in Spain, with the main objective of reducing FOF through nursing interventions in the primary care setting. This study will measure the effectiveness of the health education intervention at 1, 6 and 12 months, which means that the effect of the health education intervention will be assessed both in the short and long term.

This study protocol attempts to unify effective interventions into a single educational group intervention that could be implemented in a standardized way in the primary care setting. After a review of the relevant literature on effective interventions for this type of patient, we believe that a single intervention focusing on functional ability enhancement, fall prevention, cognitive restructuring, ability to cope, and anxiety management could represent the priority type of intervention for these patients, as reported in previous publications on the topic [3,4,9,18,19,21,22,24,35,40,41].

Moreover, the multicenter approach of this study and the data collected on these variables will help to assess the feasibility of incorporating the health education intervention into daily clinical practice.

If the health educational intervention proves effective, it could be of great value to patients living with this prevalent health problem, as it would facilitate the screening of FOF and the application of this type of intervention in nurses’ offices, thus helping to reduce long-term disability caused by voluntary activity restriction at earlier stages of life. Furthermore, the results of this study may contribute to future research aimed at addressing these issues among community-dwelling individuals over 65 years of age.

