It is also our belief that the 12-month follow-up described above may yield valuable data for future studies in this line of research, as the duration of clinical trials in this line of research is usually no longer than 6 months [17,42,43]. In addition, it is important to know whether the effect of the group-based educational intervention has a long-term impact on patients, contribute providing long-term evidence on effective health education interventions to reduce fear of falling and falls in older people living in the community. Finally, this study could be added to other studies with results after 12 months, evaluating the sum of long-term research, also encouraging long-term research.

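### The mixed model meant to assess the effect by time names no group-by-time term, so fitted as written it gives one averaged arm difference and cannot test whether the effect changes

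*Protocol article*

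**What the plan says.** All modelling statements are in Section 4.4 of the protocol article.

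- **Main analysis.** A fixed-effects ANOVA for short FES-I: "Model will include group and facility as independent variables, with facility being a nested factor within group". Effectiveness "will be measured through the decrease in the short FES-I scale scores". The measurement times follow: "assessed at three times: at 1-, 6- and 12 months after the intervention". The arms are then compared on their mean scores.
- **Analysis over time.** A separate sentence gives the purpose and the terms: "To assess the impact of the health education intervention by time, mixed effects models will be adjusted, including time also as an independent variable". Each participant also has a random intercept in this model.

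Section 2.11.1 and Table 2 have short FES-I collected at four visits: baseline and 1, 6 and 12 months. Section 2.2 places the hypothesised 3.8-point difference at 6 and 12 months. Section 5 says that "the effect of the health education intervention will be assessed both in the short and long term". It also stresses the value of learning "whether the effect of the group-based educational intervention has a long-term impact on patients".

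**The concern.** The mixed model is the only analysis given the task of describing how the intervention effect behaves over time. An effect that differs by visit is an interaction between group and visit. The sentence adds time to the list of independent variables and stops there. In an additive model the time coefficients describe the trend shared by both arms, and the group coefficient is one difference assumed equal at every visit. Neither answers the question that the model is there to answer.

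The durability of the effect is one of the trial's stated contributions. Section 4.3 also places a booster session between the 6-month and 12-month visits, so a constant effect cannot simply be presumed. Two analysts could follow the sentence and fit different models, one of which says nothing about change in effect.

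**Working it through.** **Inputs.** Difference 3.8, SD 5.1, ICC 0.1, 12 participants per facility, five facilities per arm, 80% power, 20% loss (Section 2.7). Visits from Section 2.11.1 and Table 2. Model terms from Section 4.4.

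**1. The plan's own figure.** The article gives no figure for the mixed model. Its sample size reproduces, taking alpha as two-sided (sidedness is not stated):

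- Per arm without clustering: 2 × (1.960 + 0.842)² × 5.1² / 3.8² = 28.3.
- Design effect: 1 + (12 − 1) × 0.1 = 2.1.
- 28.3 × 2.1 = 59.4 per arm, about 119 in total against 120 stated. Power with 60 per arm is 80.4%.
- 120 / 0.8 = 150.

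So 3.8 points is used below as the trial's own effect size.

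**2. What the named terms estimate.** Literal model: score = group + facility within group + visit + participant intercept + error. With complete data and equal facility sizes, the group coefficient is the plain mean of the arm differences d at the K modelled visits:

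coefficient = (d₁ + … + d_K) / K

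The expected generalised least squares estimate was also computed exactly for group, categorical visit and a participant intercept. Facility was left out, since equal facility sizes leave the arm contrast unchanged. Within-person correlations of 0.3, 0.5 and 0.77 gave the same values.

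**3. Patterns over time.** The patterns are illustrations, given as points of reduction.

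| True effect at 1, 6, 12 months | Three follow-up visits | Baseline as a fourth outcome visit |
|---|---|---|
| 3.8, 1.9, 0 (fading) | 5.7/3 = 1.9 | 5.7/4 = 1.425 |
| 0, 1.9, 3.8 (growing) | 5.7/3 = 1.9 | 5.7/4 = 1.425 |
| 1.9, 1.9, 1.9 (flat) | 5.7/3 = 1.9 | 5.7/4 = 1.425 |
| 3.8, 3.8, 3.8 (constant) | 11.4/3 = 3.8 | 11.4/4 = 2.85 |

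The first three rows cannot be told apart in either column.

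**4. The baseline condition.** The expected arm difference at baseline is zero. If baseline is an outcome visit, that zero enters the mean: 2.85 / 3.8 = 0.75, a loss of one quarter. If 20% drop out evenly over follow-up (assumption), the estimate is 2.61 to 2.69, a loss of 29% to 31%. The fading, growing and flat patterns then differ slightly (1.20 to 1.43 across all cases), but the coefficient still does not identify the pattern. If baseline is not an outcome visit, the shrinkage is zero.

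**5. Check by simulation** (ten facilities of 15, ICC 0.1, SD 5.1). Main-effects model, 100 datasets each: the constant 3.8 effect over four visits gave 2.87; fading and flat effects over three visits gave 2.00 and 1.97. With a group-by-visit interaction, 50 datasets, the fading pattern gave 4.05, 1.92 and 0.12 against true values of 3.8, 1.9 and 0. Allowing for simulation error, these agree with the algebra.

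**The case against.** Three points can be made for the plan, and each has substance.

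- **The sentence does not exclude an interaction.** It never says that time enters only as a main effect. Since its purpose is the impact by time, a statistician could take it as shorthand for a group-by-time model, and a condensed article need not list every term. This stands, so one cannot say that the plan rules an interaction out. But the sentence does list terms, and that list does not deliver the purpose given in the same sentence.
- **Differences at each visit are planned elsewhere.** The main analysis compares group means at 1, 6 and 12 months. A reader might infer that the trial as a whole cannot show whether the effect fades or lasts. The article does not support that: a fading pattern would be visible in those comparisons. What they lack is a test of whether the effect differs between visits.
- **The loss of a quarter is conditional.** A reader might infer from the four collection visits in Table 2 that the model will underestimate the effect by 25%. Table 2 shows when data are collected, not which visits are modelled, and measuring effectiveness as a decrease at three follow-up times points towards change from baseline. This stands, so the shrinkage is a risk to close off and not an error in the plan.

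The mixed model is also supplementary. The primary efficacy analysis is the ANOVA, and nothing ties the 3.8-point hypothesis to the mixed-model coefficient.

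**Conclusion.** The concern holds, limited to the supplementary mixed model and to the formal assessment of change in effect over time. The terms named for that model give one averaged arm difference. With complete data, effects with the same mean over visits give the same coefficient whether they fade, stay flat or grow. The result rests on reading the listed terms literally, complete data and equal facility sizes; it does not depend on the within-person correlation.

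The drop from 3.8 to 2.85 applies only if baseline short FES-I is an outcome visit with the group term acting on it. The article leaves that open. These figures concern short FES-I; for falls, the missing interaction matters in the same way, but the baseline dilution is not claimed. The primary ANOVA and the planned comparisons at each visit are not affected.

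**What to change.** In Section 4.4, replace the mixed-model sentence with one stating that:

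- short FES-I at 1, 6 and 12 months is modelled with group, visit as a categorical factor and a group-by-visit interaction, keeping the participant random intercept;
- baseline short FES-I enters as a covariate, or alternatively as a visit at which both arms are constrained to a common mean, so that it cannot dilute the group term;
- the arm difference with 95% CI is reported at each visit;
- any claim about change in effect over time rests on the interaction and the 12-month contrast, not on a single group coefficient.

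This takes a few lines of wording and uses data already collected. The downside is small: visit-specific estimates are less precise than a pooled one. The trial was also sized for an arm difference and not for the interaction, so a non-significant interaction should not be read as proof of a constant effect.
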